## Abstract

**Background:**

Cerebral palsy (CP) is frequently associated with specific cognitive impairments, such as executive dysfunction which are related to participation and quality of life (QOL). The proposed study will examine whether a computerized executive function (EF) training programme could provide superior benefits for executive functioning, participation, QOL and brain plasticity, as compared to usual care.

**Methods:**

A single-blind randomized controlled trial (RCT) design will be performed. Thirty children with CP aged 8 to 12 years will participate in a home-based computerized multi-modal executive training programme (12 weeks, 5 days a week, 30 min a day training, total dose = 30 h). Thirty children with CP matched by age, sex, motor and intelligence quotient (IQ) will compose the waitlist group. Cognitive, behavioural, emotional, participation and QOL measures will be obtained at three time points: before, immediately after and 9 months after completing the training. Additionally, structural and functional (resting state) magnetic resonance images (MRI) will be obtained in a subsample of 15 children from each group. Outcomes between groups will be compared following standard principles for RCTs.

**Discussion:**

The study will test whether the cognitive training programme exerts a positive effect not only on neuropsychological and daily functioning of children with CP but also on other measures such as participation and QOL. We will also use brain MRI to test brain functional and structural changes after the intervention.

If this on-line and home-based training programme proves effective, it could be a cost-effective intervention with short- and long-term effects on EF, participation or QOL in CP.

**Trial registration:**

ClinicalTrials.gov: NCT04025749. Registered 19 July 2019. Retrospectively registered.

## Background

Cerebral palsy (CP) describes a group of permanent disorders of the development of movement and posture, causing activity limitations that are attributed to non-progressive disturbances that occurred in the developing fetal or infant brain [1]. At present, CP is the leading cause of physical disability in children, with a prevalence of two or three out of every thousand newborns [2]. As a chronic condition, individuals with CP usually require lifetime medical, psychological, educational and social support [3]. People with CP present with alterations in sensation, perception, cognition, communication and behaviour that hinder activities of daily life, participation and quality of life (QOL) [1, 4, 5].

Cognitive functioning is the result of a complex interplay between neurological, motor and communication processes as well as environmental support over time [6]. The neuropsychological profile in CP is heterogeneous with a high prevalence of visuospatial [7] and executive function (EF) deficits [6]. Regarding EF, some studies have highlighted lower performance in sustained attention, working memory, inhibition, processing speed, metacognition and strategic planning [5, 6, 8, 9].

Executive functions play an important role in behaviour regulation, social abilities and performance of activities of daily living. In this way, poor executive functioning may lead to slower social development and behavioural problems. Executive functioning is also essential for social problem solving and emotional regulation in children and young people with CP [3, 9]. EF has been shown to play an important role in the QOL of people with CP [10].

### Home-based multi-modal computerized training in CP

Research in CP to date has mainly focused on medical- and movement-related interventions [11]. Cognitive interventions are however also needed given that cognitive impairment such as executive dysfunctions is usually associated with CP and may be related to participation and QOL.

Most current interventions require the participant to travel to receive their training, which may reduce adherence and efficacy, especially in people with motor disorders. Alternative EF home-based therapies, such as internet-delivered programmes or active videogames, are emerging as a popular modality to increase participants’ motivation [12]. Some authors suggest that home-based computerized cognitive training has the potential to deliver novel, engaging and intensive therapies to children that could improve EF performance and participation in more complex activities and their QOL [3, 4]. Computerized EF training has been demonstrated to improve EF domains such as inhibition, working memory and visuoperceptual processing in children born preterm, or with medical conditions such as Attention deficit hyperactivity disorder (ADHD), arterial ischaemic stroke, cranioencephalic trauma or cancer [13–17].

Similar results have been found in adults after computerized therapies [18–22].

According to Diamond there are three core EFs (inhibition, working memory and cognitive flexibility) and from these, higher-order EFs are built (reasoning, problem solving and planning & monitoring) [23]. There have been some home-based randomized controlled trials (RCT) in children with CP focused on a single domain of EF such as working memory using the Cogmed System [24] and attention using the MiYoga Programme [25]. Previous studies in other populations indicate that training more than one EF domain allows the transference of improvements to other cognitive functions or clinical symptoms [26, 27]. For this reason, multi-modal tasks might better allow the transference of abilities across EF domains; EF interventions should consider all components and their developmental trajectories [27].

The transference effect from motor to cognitive functions has previously been tested in the CP population. Piovesana [28] used a home-based multi-modal computerized training programme designed to improve motor skills in children with CP. They were however unable to demonstrate improvements in EF performance. Some studies that used interactive training to improve motor skills in participants with CP found changes in visuoperceptual functions [29, 30]. There is a lack of studies with long-term follow-up in this field: to our knowledge, only one study [29] has measured long-term changes in cognition (visuoperceptual function) in children with CP.

### Magnetic resonance imaging (MRI) related to cognitive function training

Measuring the changes in neuroplasticity promoted by therapy would involve understanding how and for whom rehabilitation could be effective [31]. Connectivity techniques involving diffusion MRI (dMRI) and the resting state in functional MRI (fMRI) [31, 32] have been used after motor-focused interventions in people with unilateral CP to analyse and quantify improvements. New techniques in neuroimaging might allow an understanding of the neural reorganization that occurs after a neuropsychological intervention [33].

Horowitz-Kraus [34] found that children with lector deficit increased brain activation and compensatory brain reorganization between visual and EF networks after improvements in reading skills promoted by/following computerized training. Changes in cerebral connectivity in the frontoparietal and occipital cortex networks, as well as neural connectivity changes, have also been found after cognitive training in healthy children [35–37]. Finally, Conklin [13] found changes in cerebral functioning with a reduction in the activation of the prefrontal medium and lateral cortex in children with cancer after training. In adults, some studies have found brain structural and functional changes in healthy participants after an intervention. Specifically, Eggenberger [22] induced modulations in prefrontal cortex oxygenation that were associated with improvements in EF. Another study found that exercise dose was associated with increased brain-derived neurotrophic factor as well as increased grey matter volume in the prefrontal and anterior cingulate cortices [38]. This study also found that memory improvements were associated with an increase in the volume of the dorsolateral prefrontal cortex.

## Methods

This aim of the proposed study is to conduct a single-blind RCT with 60 children with CP to assess whether a home-based computerized multi-modal training programme might be effective at improving infants’ EF, as the primary outcome. As secondary outcomes, the study will test whether the computerized therapy exerts a positive effect on other cognitive functions and other areas such as participation and QOL in children with CP. It is further expected that structural and functional brain changes might be observed.

The primary hypothesis to be tested is:
The computerized multi-modal cognitive training programme will be more effective than usual care alone at improving executive functioning in children with CP.

The secondary hypotheses are that the computerized multi-modal cognitive training programme will be more effective than usual care at improving the following outcomes in children with CP.

The computerized multi-modal cognitive training programme will be more effective than usual care at improving the following outcomes in children with CP:
Visuoperception and memory due to the transference effect.Participation.QOL.Structural and functional brain changes due to brain plasticity.

The long-term efficacy of the intervention will be checked. Finally, the effect of other variables such as the main sociodemographic and clinical factors on the efficacy of EF training will be evaluated.

### Participants

The sample will consist of 60 children with CP. These participants will mainly be recruited from the Hospital Vall d’Hebron, the Hospital Sant Joan de Déu and the Cerebral Palsy Association ASPACE in Barcelona.

#### Inclusion criteria

Aged 8–12 years.Manual Abilities Classification System (MACS) ranging from I to III [39].Intelligible yes/no response system.Ability to understand simple instructions as evaluated using the Screening Test of Spanish Grammar [40].Availability to participate in the investigation for 1 year.Accessibility to the internet at home.

Participants who have no metallic prostheses, brain shunts, claustrophobia or other factors that prevent the application of neuroimaging will be prioritized to undergo scanning.

#### Exclusion criteria

Identified hearing or visual impairment that precludes neuropsychological assessment and cognitive training.

### Procedure

Participants will be contacted by the medical staff of their reference health centre. Then, researchers will provide participant information and seek informed consent at a first interview at their reference health centre or in the study setting at the Faculty of Psychology, University of Barcelona (UB).

Assessments will be carried out at the University of Barcelona and neuroimaging will be performed at the Hospital Sant Joan de Déu. The intervention will take place in each participant’s home, with monitoring and support from an experienced neuropsychologist.

### Design

This study is researcher-blinded and will be a pair-matched and randomized waitlist controlled trial. Demographic data and motor, communication and other associated deficit measures will be collected at the first interview after participants’ parents or guardians and children have provided informed consent. Detailed information about the methodology and timing of assessments is shown in Fig. 1. The waitlist design will ensure that all participants have access to this novel intervention by assigning each participant to either Group 1 (immediate intervention) or Group 2 (waitlist */* delayed intervention)*.*

**Fig. 1 Fig1:**
[figure not shown]
D-KEFS: Delis-Kaplan Executive Function System; MRI: Magnetic Resonance Imaging; NEPSY-II: A Developmental NEuroPSYchological Assessment-II; TOMAL: Test of Memory and Learning; WISC-V: Wechsler Intelligence Scale for Children, Fifth Edition; WNV: Wechsler Nonverbal Scale of Ability

After baseline assessments (T0, Additional file 1), the Group 2 will continue care as usual for 12 weeks, whilst the Group 1 will receive usual care as well as home-based multi- modal cognitive training for 12 weeks (30 min/day, 5 days/week, total of 30 h). Both groups will be assessed after these 12 weeks (T1). A follow-up assessment will be performed 9 months after T1 (T2). After this assessment, Group 2 will have access to the same conditions as Group 1.

Patients or the public were not involved in the design, or conduct, or reporting, or dissemination of our research.

### Sample size determination

The required sample size was calculated by taking into account the differences in the continuous primary outcomes after 12 weeks of following the computerized training programme. Simulations under two different scenarios were carried out. Specifically, calculations for separate tests and multiple-end-points were performed. By comparing the two scenarios, conservative figures regarding sample size were estimated. As a result, to detect a large standardized difference (i.e. a difference of at least 0.8 SD) between the immediate intervention and waitlist groups, with 80% power and α = 0.05, 26 children would be necessary in each group. Assuming 15% attrition, the required sample size was calculated as 60 participants.

### Blinding

Single blinding will be applied to the researcher that performs the cognitive assessment as well as those in charge of the statistical analyses. Thus, code identification will be used for the two groups, ensuring that correspondence between codes and group characteristics (i.e. immediate intervention or waitlist) is not known by the aforementioned individuals.

### Adverse events

Any minor or major events associated with the intervention or usual care groups will be screened every week through open-ended questions. Any adverse events or unintended effects detected will be reviewed by a researcher.

### Equipment

The cognitive training programme requires no specialized resources other than an internet connection. All participants will receive a password to access the home-based computerized multi-modal training programme.

### Computerized multi-modal cognitive training

Neuron Up (www.neuronup.com) is the cognitive training and stimulation programme that will be used. It covers all levels of difficulty of all EF domains. Table 1 shows some examples of the tasks. The training programme will also include some cognitive tasks based on activities of daily living that may promote generalization. The programme is delivered via the internet, providing the possibility of monitoring the participants’ performance in real time.

**Table 1 Tab1:**
[figure not shown]
Examples of multi-modal activities in home-based computerized cognitive training programme

A participants’ instruction manual explaining how the training programme works, and providing contact information and motivational strategies to encourage engagement in the cognitive training programme, will be delivered to each participant. A trainer will be able to monitor each participant’s training, and record important data such as how frequently the participant has logged into NeuronUp, how long they have spent engaged in the therapy, their training progress and their level of motivation. Neuropsychologist will contact each participant’s family weekly in order to give feedback on the recorded information.

### Data management

All collected data will be managed through a confidential online database run through the Universitat de Barcelona. Files containing information from the participants will be stored in a locked filing cabinet at the Universitat de Barcelona. Each participant will use a personal ID to log into NeuronUp, and the study researcher who will contact the families and follow up the training (neuropsychologist) will be different from the researcher that performs the cognitive assessment.

### Assessments

Figure 1 shows the neuro-psycho-social assessments that will be performed at T0, T1 and T2. Effort has been made to select cognitive measures that are free of motor and speed components. Several domains of EF, as well as visuoperception, memory, participation and QOL will be assessed. The measures used are standardized and validated for use across a wide age range and have good retest reliability (Additional file 1).

As Sabbadini [41] advised, participants will be encouraged to answer by themselves, but some accommodations will be used if necessary, taking into account the experience of previous studies [42].

### MRI acquisition

Neuroimaging will be performed at T0, T1 and T2. Participants will be prepared for the imaging sessions in order to optimize the quality of images acquired. This preparatory session will consist of explaining the procedure, familiarization with the facilities and finding entertainment strategies adapted to each participant.

Structural, functional, and diffusion MR images will be acquired on a Phillips Ingenia 3.0 T scanner. These sequences have been harmonised with several other studies [43–46] in order to maximise their utility and interpretability [47].

Structural imaging includes high resolution T1w MPRAGE (FOV 256 mm; acquisition matrix size 256 × 255; reconstruction matrix size 256 × 256; 192 slices; slice thickness 1 mm; TR 2500 ms; TE 3.0 ms; flip angle 9°; SENSE acceleration factor: RL 2) and high resolution T2w FLAIR (FOV 256 mm; acquisition / reconstruction matrices sized 256 × 256; 192 slices; slice thickness 1 mm; TR 5000 ms; TE 388 ms; SENSE acceleration factors: AP 1.4, RL 2).

The diffusion weighted imaging protocol is a multishell sequence (FOV 240 mm; acquisition matrix size 96 × 94; reconstruction matrix size 96 × 96; 60 slices; slice thickness 2.5 mm; TR 8778 ms; TE 115 ms; flip angle 90°; SENSE acceleration factor: AP 2). The acquisition includes 8x non-diffusion weighted images (b = 0 s/mm^2^) as well as 20 (b = 1000s/mm^2^) and 60 (b = 3000 s/mm^2^) unique directions. These are split across four blocks with alternating AP/PA phase encoding directions for the purpose of post-acquisition distortion correction. Acquiring images across four blocks also allows technicians to re-acquire portions of sequence if the child moves during acquisition, rather than requiring re-acquisition of the full sequence.

A resting state fMRI will also be acquired (FOV 240 mm; acquisition matrix size 80 × 78; reconstruction matrix size 80 × 80; 40 slices; slice thickness 3 mm; TR 2300 ms; TE 30 ms; SENSE acceleration factor, AP 2; 266 frames). Participants will be asked to remain still and relaxed with their eyes closed for the total duration of this scan.

### Statistical analysis

Statistical analysis will follow standard principles for RCTs (e.g. running sensitivity analysis with non-ignorable missing data). Primary and secondary outcomes will be summarized for each group depending on the measurement scale and data distribution (frequencies, means, SDs, medians, IQRs, 95% CIs). To assess training effectiveness, parametric (or nonparametric, depending on the data distribution) tests will be used for the groupwise comparisons after the 12th week (post-intervention; T1). Comparisons between groups at follow-up (after 9 months; T2) will be made using Generalized Estimating Equations (GEEs). The fixed factors are time (week 0, 12, and 36), group (immediate and waitlist), and time by group interaction. Assuming a Gaussian distribution for the outcomes, identity link functions will be used. Given the small sample size and in order to avoid possible numerical problems, we will reduce the complexity of the model by using an exchangeable working correlation matrix. Statistical significance will be considered at *p* < .05 and post-hoc adjustment will be applied for multiple comparisons. All data will be treated following an intention-to-treat approach and multiple imputation will be used for treating missing data whenever possible.

Finally we will compare neuroimaging data achieved from structural sequences as T1w, T2w FLAIR and dMRI and functional acquisitions between the groups and with each other. For this purpose appropriate preprocessing and adequate analysis of data will also be performed.

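### The T1 test family is left to the observed data distribution, so the primary hypothesis can differ between executive function outcomes and from the mean difference used for sizing

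*Protocol article*

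**What the plan says.** All of the following is in the protocol article.

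- **T1 comparison (Statistical analysis).** "parametric (or nonparametric, depending on the data distribution) tests will be used for the groupwise comparisons after the 12th week (post-intervention; T1". No criterion for the choice and no test name is given. The text does not say whether the choice is made once or outcome by outcome.
- **T2 comparison (same section).** A GEE with time, group and their interaction, whose time factor includes week 12: "Assuming a Gaussian distribution for the outcomes, identity link functions will be used".
- **Missing data (same section).** After an intention-to-treat statement, "multiple imputation will be used for treating missing data whenever possible".
- **Primary outcome (Methods).** The question is whether the training "might be effective at improving infants’ EF, as the primary outcome". The Assessments section says that several EF domains are measured.
- **Sizing (Sample size determination).** It rests on "differences in the continuous primary outcomes after 12 weeks of following the computerized training programme", planned "to detect a large standardized difference (i.e. a difference of at least 0.8 SD) between the immediate intervention and waitlist groups".
- **Blinding.** The analysts see group codes but do not know which code is which arm.

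**The concern.** T1 is where the primary hypothesis is tested, and the article commits that test to a family picked after the data are seen. A t-type test compares means. The usual nonparametric alternative compares ranks, which is a different hypothesis once the arms differ in spread or shape. With several EF outcomes, some could be judged on one quantity and some on the other, and only the first can be set against the 0.8 SD used for planning.

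Two further difficulties follow from the same rule. An outcome could be called non-normal for its T1 test and then enter, T1 values included, a model that treats it as Gaussian. And an outcome moved to an ordinary rank test has no obvious route through multiple imputation.

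At stake are a fixed estimand for the primary comparison, freedom from analyst discretion, and precision that a model using the T0 score and the matching could give.

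**Working it through.** **1. The plan's own figure.** Inputs from Sample size determination: 0.8 SD, 80% power, α = 0.05 (two-sided assumed), 15% attrition.

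- Normal approximation: n = 2 × (1.960 + 0.842)² / 0.8² = 24.5, so 25 per group.
- Two-sample t-test (noncentral t): 25.5, so 26 per group, with power 0.807 at 26. This reproduces "with 80% power and α = 0.05, 26 children would be necessary in each group".
- Attrition: 52 × 1.15 = 59.8, so 60 as stated. (52 / 0.85 = 61.2 would give 62; nothing here turns on that.)

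The stated 26 is therefore what a comparison of means needs. A Mann-Whitney test on normal data would need 25.5 / 0.955 = 26.7, so 27.

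**2. What the rule does.** The article names no criterion, so one must be assumed: Shapiro-Wilk at 0.05 in each arm, Mann-Whitney if either arm fails, otherwise the t-test. Simulation with 26 per arm and 8,000 trials per setting (Monte Carlo SE near 0.05 is √(0.05 × 0.95 / 8000) = 0.0024):

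| Distribution (assumed) | Switches to ranks | Type I error: rule / smaller of the two p-values | Power at 0.8 SD: t / Mann-Whitney / rule | Tests disagree at 0.8 SD |
|---|---|---|---|---|
| Normal | 10% | 0.050 / 0.057 | 0.801 / 0.777 / 0.801 | 5.8% |
| t, 5 df | 40% | 0.047 / 0.060 | 0.804 / 0.862 / 0.852 | 8.4% |
| Lognormal, σ = 0.5 | 88% | 0.054 / 0.067 | 0.811 / 0.914 / 0.913 | 11.6% |
| Exponential | nearly 100% | 0.046 / 0.062 | 0.812 / 0.948 / 0.948 | 14.0% |

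Gamma data under the same criterion switch in about 23 to 24% of trials at skewness 0.5, 38% at 0.7, 62% at 1.0 and 92% at 1.5.

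**3. Mixed families across outcomes.** In a separate run with normal data the switch probability was q = 0.0925. For m independent outcomes (an assumption; the article gives no number), P(both families used) = 1 − q^m − (1 − q)^m.

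- m = 3: 1 − 0.0008 − 0.7474 = 0.25.
- m = 5: 1 − 0.00001 − 0.6155 = 0.38.

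**4. Whether the rule still tests the mean difference.** Equal means, SD ratio 2 (assumed), skewed data:

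| Distribution | t-test rejects | Mann-Whitney rejects | Rule rejects |
|---|---|---|---|
| Lognormal | 0.052 | 0.128 | 0.126 |
| Exponential | 0.062 | 0.228 | 0.228 |

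With no difference in means, the rule rejects in 12.6% to 22.8% of trials. It is then answering a question about ranks, not the one on which the trial was sized.

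**5. Imputation.** Rubin's rules combine an estimate Q_j and its variance U_j from each of m completed data sets: the pooled estimate is the mean of the Q_j, and the total variance is the mean of the U_j plus (1 + 1/m) times the variance of the Q_j. The t-test branch supplies both. An ordinary rank test supplies a statistic and a p-value, so it cannot be entered directly.

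**6. Precision.** The article does not say that the T1 test uses the T0 score or the pairs. For illustration, a paired t-test at 0.8 SD needs 26.5, 19.2 or 14.3 pairs (27, 20 or 15 rounded up) if the within-pair correlation is 0, 0.3 or 0.5. These correlations are assumed; the article gives none.

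**The case against.** The best defence has five parts.

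- **Type I error is sound.** With equal distributions the mechanical rule gives 0.046 to 0.054. This stands. Even taking the smaller p-value each time gives only 0.057 to 0.067, and analysts blinded to the codes cannot readily steer the choice towards the intervention.
- **Ranks can gain power.** For a pure shift in skewed data, Mann-Whitney reaches 0.91 to 0.95 against 0.81 for the t-test. This also stands, but it argues for a rank analysis fixed in advance, not for a choice made from the data.
- **The two modelling sentences can coexist.** A reader might infer that the T1 rule contradicts the Gaussian T2 model. It does not. The sentences govern different analyses, and inference on means from a GEE with robust standard errors does not need normal data. What remains is an inconsistency: two week-12 comparisons of one outcome, possibly on different scales.
- **Imputation is hedged.** A reader might infer that the imputation plan cannot be carried out. The article limits it to where it is feasible, the parametric branch pools directly, and a rank-based estimate with its standard error can be pooled. Nor does nonparametric have to mean a rank test. A reader might also count 60 × 0.15 = 9 children as lost to the primary test, but a complete-case fallback is nowhere stated, and that attrition is already budgeted: 60 − 9 = 51, about 25.5 per arm, with t-test power of about 0.80.
- **Detail belongs in the SAP.** Test names and normality criteria may well be there, and their absence from an article is no fault. But the article does more than omit them. It states a data-dependent rule, and an SAP that fixed one test would have to depart from it.

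**Conclusion.** The point holds at moderate weight. The article fixes the primary T1 analysis badly: the quantity tested may vary between EF outcomes and may not be the mean difference behind the 26 per group.

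Under the assumed criterion, about one normal outcome in ten would switch, as would about a quarter at skewness 0.5 and 62% at 1.0. At 0.8 SD the choice of test changes the significance verdict in 5.8% to 14.0% of trials. It would be too strong to call the switch arbitrary in general: detection is 92% at skewness 1.5, and chance decides mainly in the mild to moderate range. The 12.6% to 22.8% rejection rates depend on skewed data with an SD ratio of 2, which nothing in the article suggests; they show that the hypotheses differ, not what to expect here.

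The cost is an unfixed estimand, room for discretion and forgone precision. It is not a material loss of type I error control. All simulated figures rest on the assumed criterion, distributions and 26 per arm.

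**What to change.** Drop the data-dependent choice and name one T1 analysis for every continuous outcome: the difference in means from a linear model with the T0 score as covariate, accounting for the matching (matching variables as covariates, or pair as a model term or cluster), pooled over imputations by Rubin's rules. Heteroscedasticity-robust errors alone would not deal with the pairing.

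Keep a rank-based or within-pair permutation analysis as a sensitivity check only. Because its p-value has the same pooling limitation, state beforehand on which data it will be run.

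The cost is wording; no new data are needed, and 26 per group stands (power 0.807 for the unadjusted t-test). There are two downsides. For a strongly skewed or ceiling-limited score the mean difference describes the effect less well, which the medians and IQRs already planned will cover. And for a pure shift in skewed data the extra power of a rank test is given up, although the mean comparison kept about 0.81 in the settings above.

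### As most naturally read, the primary T1 test uses neither the T0 score nor the matched pairs, so it is valid but gives up precision that costs almost nothing to recover

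*Protocol article*

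**What the plan says.** The protocol article's Statistical analysis section handles the two post-baseline time points differently. For T1, the time point on which the trial is sized, parametric or nonparametric "tests will be used for the groupwise comparisons after the 12th week (post-intervention; T1"). No covariate, change score or pair term is named. For T2, "Comparisons between groups at follow-up (after 9 months; T2) will be made using Generalized Estimating Equations (GEEs"), and for that model "The fixed factors are time (week 0, 12, and 36), group (immediate and waitlist), and time by group interaction". This is the only place where week 0 enters an analysis.

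Baseline scores will be available. The Abstract says that "measures will be obtained at three time points: before, immediately after and 9 months after completing the training", and the Assessments section says "Figure 1 shows the neuro-psycho-social assessments that will be performed at T0, T1 and T2". That section also describes the measures as ones that "have good retest reliability (Additional file 1"), without giving a figure in the text shown.

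The Randomization section matches children in pairs on four factors (age, sex, IQ, manual ability) and allocates within each pair. Baseline executive function is not a matching factor. The Sample size determination section targets "a difference of at least 0.8 SD" with 80% power at α = 0.05. It gives 26 per group, and 60 in total after 15% attrition.

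**The concern.** The primary hypothesis concerns improvement in executive function, and a child's T0 score on the same test is likely to be the best single predictor of the T1 score. A two-group comparison of T1 scores leaves all of that between-child variation in the error term. It also lets a chance T0 difference between arms pass into the estimated effect in proportion to r, the T0-T1 correlation.

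With about 25 children per arm, neither effect is negligible if r is moderate or high. Unadjusted, the trial has good power only for a large effect. Allocation within pairs is a second source of precision that an unpaired test does not use.

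**Working it through.** **Inputs.** From Sample size determination: difference 0.8 SD, power 80%, α = 0.05 (sidedness not stated), 26 per group, 15% attrition, total 60. Expected completers per arm: 60 × 0.85 / 2 = 25.5. Assumption: r is not in the documents, so 0.3, 0.5 and 0.7 are shown. A measure's retest reliability is not the same as its T0-T1 correlation over 12 weeks in these children, so "have good retest reliability" does not fix r.

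**Step 1: the plan's own figure.** A two-sided two-sample t-test at 0.8 SD with 80% power needs 25.5 per arm, so 26 (power 80.7%). A one-sided test needs about 20 by the normal approximation, which does not match. The stated 26 is therefore reproduced without any baseline adjustment.

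**Step 2: precision with T0 as covariate.** With the T1 SD set to 1, the variance of the group difference is 2/n unadjusted and 2(1 − r²)/n adjusted. Power comes from the noncentral t with 49 degrees of freedom unadjusted and 48 adjusted, at n = 25.5 per arm:

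| Analysis | 1 − r² | SE | Power at 0.8 SD | Power at 0.5 SD | Detectable at 80% power |
|---|---|---|---|---|---|
| T1 only | 1 | 0.280 | 80.0% | 41.7% | 0.80 SD |
| T0 adjusted, r = 0.3 | 0.91 | 0.267 | 83.5% | 45.0% | 0.76 SD |
| T0 adjusted, r = 0.5 | 0.75 | 0.243 | 89.8% | 52.4% | 0.69 SD |
| T0 adjusted, r = 0.7 | 0.51 | 0.200 | 97.5% | 68.8% | 0.57 SD |

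To match the adjusted analysis, a T1-only test would need n/(1 − r²) per arm: 25.5/0.91 = 28, 25.5/0.75 = 34 and 25.5/0.51 = 50.

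**Step 3: chance imbalance.** Ignoring the matching, the T0 difference between arms has SD √(2/25.5) = 0.28 SD. It exceeds 0.3 SD in about 28% of trials and 0.5 SD in about 7%. A fraction r of it carries into the T1 difference. For example, an imbalance of 0.5 SD at r = 0.7 contributes 0.5 × 0.7 = 0.35 SD, against a target of 0.8 SD.

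**Step 4: allowing for the matching.** A simulation used 26 per arm, 4,000 runs per setting and a true effect of 0.5 SD. It let the matching explain none, 30% or 50% of the baseline variance. Results for the 50% setting:

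| r | SD of T1-only estimate | SD of T0-adjusted estimate | Power: unpaired t | Power: paired t | Power: T0 adjusted |
|---|---|---|---|---|---|
| 0.5 | 0.261 | 0.243 | 42% | 46% | 53% |
| 0.7 | 0.242 | 0.199 | 40% | 49% | 68% |

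With no matching effect, the T1-only SD was 0.278 at both values of r. Matching therefore does reduce the imbalance, but an unpaired test gains no power from it, and the T0 score still adds precision.

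**The case against.** **The premise is an inference.** The protocol does not say that baseline is ignored. The word tests could be stretched to cover analysis of covariance, and a hypothesis about improvement could mean change scores. The reproduced sample size does not settle this, because a t-test on change scores standardized by their own SD gives the same 26. This stands as a limit on certainty. Even so, the article names a method for T1 and a different one, containing week 0, for T2. A t or rank test at T1 is the most natural reading. Change scores would not remove the point either. Their variance relative to a T1-only test is 2(1 − r), that is 1.4, 1.0 and 0.6 at r = 0.3, 0.5 and 0.7, against 0.91, 0.75 and 0.51 with T0 as covariate.

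**Nothing fails without adjustment.** This is correct. Randomization keeps the unadjusted test valid and unbiased on average, and its standard error already allows for chance imbalance. A reader might infer that the primary test is biased or the trial underpowered for its target. The documents support neither.

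**Matching already balances the arms.** This holds in part. IQ and age plausibly correlate with executive function, so imbalance should be smaller than Step 3 shows. Step 4 indicates that a gain remains.

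**Two answers for T1.** A reader might infer that the primary effect receives two competing estimates, because the GEE also contains week 12. The text does not say so. It assigns T1 to the test and T2 to the GEE, and nothing states that a week-12 GEE contrast will be reported as the T1 effect.

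**Conclusion.** The point holds as a question of efficiency. On the most natural reading, the primary T1 comparison uses neither the T0 score nor the pairs. With r between 0.3 and 0.7 and 25.5 completers per arm, T0 adjustment would raise power at 0.8 SD by about 4 to 17 percentage points. It would lower the detectable effect by about 0.04 to 0.23 SD and remove the part of the estimate due to T0 imbalance. The gain is small at r = 0.3 and substantial at 0.7. All of these figures depend on an r that the documents do not give, and those of Steps 2 and 3 also on setting the matching aside.

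The planned sample size is not shown to be wrong, and the validity of the test is not in question. This is a nearly free improvement, not the correction of an error.

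**What to change.** State that the primary T1 comparison is a linear model of the T1 score on group with the T0 score of the same measure as covariate, and that the model accounts for the matched pairs or includes the matching factors. A longitudinal model that keeps T0 as an outcome but constrains the baseline means to be equal across arms, with the effect taken from its week-12 contrast, serves the same purpose. The choice between the two is a preference. Keep the unadjusted or rank test as a sensitivity analysis, and fix the wording before group codes are broken.

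The cost is a change of wording and a few degrees of freedom: one for T0, plus those for the pairs or matching factors. Using pair effects instead of the four factors would take more. No new data and no additional children are needed.
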